### Statistical analyses

Analyses will be intent-to-treat (ITT). Any missing values for the primary endpoint will be computed by the multiple imputation method. In which case, the robustness of the conclusions made on observed cases will be verified and a possible discrepancy will be analysed based on any biases in data collection that may have been identified.

Descriptive analyses will provide the following information for each continuous variable: mean value, standard deviation, 95 % confidence intervals (95 % CI), minimum, 1st quartile, median, 3rd quartile and maximum, and number of missing observations. Categorical variables will be summarised in frequency tables (with 95 % CI). Intracluster correlation coefficients will be calculated.

The primary endpoint will be tested using the Generalised Estimating Equations model, account being taken of the cluster trial design. Secondary continuous endpoints will be analysed with a mixed-model ANOVA including a random centre effect. For categorical variables, treatment effect will be tested using the Generalised Estimating Equations model, account being taken of the cluster trial design. All tests will be two-tailed with a 5 % alpha risk. All statistical tests will be performed using SAS version 9.2 software.

The health economic analysis will consider total cost, hospital costs, ambulatory costs, cost borne by the family and costs to society. Analysis of management costs in both study arms will be ITT. Cost comparisons will be performed using appropriate statistical methods after determining the type of distribution (normal, log normal or beta).

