## Methods/design

### Design

This is a prospective open-label, multicentre, pragmatic, cluster randomised clinical trial involving six participating centres (SAMU). The centres are randomised into two arms (1:1) according to call management method, either an offer of fTMA (intervention arm) or usual after-hours medical care (control arm). Out-of-hours is 8 p.m. to 7.59 a.m. on weekdays, 1 p.m. to 7.59 a.m. on Saturdays and round-the-clock on Sundays and school holidays. Callers/patients will be randomly selected before inclusion (see Fig. 1 for the study flowchart).

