### Sample size

We postulate that fTMA will reduce the percentage of out-of-hours on-duty GP consultations or the number of visits to an ED during the 2 weeks following the index call. In the study by Lattimer et al., the percentage of hospital admissions and ED visits was 12 % after a nurse telephone consultation [17]. In a parallel study, Thompson et al. reported a 21 % versus a 33 % overnight call rate resulting in a home visit by a duty GP in the nurse telephone intervention arm versus the control arm [18]. We estimate that the percentage of out-of-hours consultations and ED visits (our primary endpoint) will be 50 % in the control group. We aim for an absolute reduction of at least 10 % (i.e. from 50 to 40 %) in the intervention arm for each indication (fever/gastroenteritis).

On the assumption of a relatively low weak design effect due to cluster randomisation (about 1.5), and considering a loss of follow-up of 15 %, it is estimated that a sample size of 663 patients/arm/indication will be required for 85 % power and a 5 % alpha risk. If account is taken of an attrition rate of about 8 %, 720 patients will be required (1440/indication, i.e. a total of 2880 patients). This sample size should provide enough power and precision for subgroup analyses (season versus diurnal cycle, weekend versus weekdays).

Inclusions will take place over a full year in order to obtain a representative sample. Each centre will thus include about 240 patients for each indication. A random sample of four patients per week will be drawn outside of an epidemic (about 42 weeks) and of eight patients per week during an epidemic (about 10 weeks) in each centre for each indication. For feasibility reasons, the first patient whose call is closest to the dates and times that will have been randomly drawn for each week of the year of study will be included for each indication.

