## Discussion

This trial will assess the effectiveness and the cost-effectiveness of a formalised response to calls made for assistance with fever or symptoms of gastroenteritis without seriousness criteria. The inclusion period ended in July 2016. The follow-up is still running and the economic evaluation will start shortly. Two of the centres had several difficulties in enrolling patients. One centre because of a lack of calls made for symptoms of gastroenteritis and the other because of an organisational problem not attributable to the trial. To analyse a potential seasonality effect, the recruitment period stopped at 12 months, as described in the methods section, even if centres had not reach the number of included patients.

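### The primary GEE test rests on six centres (3 vs 3) with no small-sample method named: run in the usual uncorrected way its type I error is about 18%, and no variant checked gives both 5% alpha and 85% power

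*Protocol article*

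**What the plan says.** The Design section describes a "cluster randomised clinical trial involving six participating centres (SAMU") and adds: "The centres are randomised into two arms (1:1) according to call management method". That is three centres per arm.

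The Statistical analyses section fixes the primary test: "The primary endpoint will be tested using the Generalised Estimating Equations model, account being taken of the cluster trial design". Categorical secondary endpoints are to be tested the same way. The level is also fixed: "All tests will be two-tailed with a 5 % alpha risk". On implementation there is one further sentence: "All statistical tests will be performed using SAS version 9.2 software". The article does not say whether the variance is robust or model-based, whether the test is Wald or score, whether the reference is z or t, or whether any small-sample correction applies.

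The Sample size section assumes that the event percentage ("our primary endpoint) will be 50 % in the control group"). The target is: "We aim for an absolute reduction of at least 10 % (i.e. from 50 to 40 %) in the intervention arm for each indication". With a design effect of about 1.5, 85% power and 5% alpha, it arrives at 663 patients per arm per indication, raised to 720 for about 8% attrition. Each centre is to supply about 240 patients per indication.

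The Discussion reports: "Two of the centres had several difficulties in enrolling patients". It gives no numbers for either centre.

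**The concern.** Allowing for clustering in a GEE deals with correlation within centres. It does not deal with having only six independent units. The usual robust variance is justified when the number of clusters is large. With three centres per arm it is built from three centre deviations per arm, so it is biased low and very variable, and a normal reference ignores both faults.

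The primary comparison for each indication, and every categorical secondary comparison, rests on this method. A null effect could be declared significant (in either direction) more than three times as often as the plan claims, and 95% confidence intervals would cover well below 95%.

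The sample size has the matching weakness. It uses large-sample normal theory inflated by a design effect, with no allowance for the 4 degrees of freedom left for the between-arm comparison.

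**Working it through.** **Inputs.** Six centres, 1:1 (Design). Two-sided 5% (Statistical analyses). 50% vs 40%, design effect 1.5, 85% power, 663 and 720 per arm per indication, about 240 per centre per indication (Sample size). The implied intracluster correlation is 0.5/(240 − 1) = 0.0021.

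**1. The plan's own figure.** Two proportions, pooled variance under the null, no continuity correction:

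n = [1.96 × √(2 × 0.45 × 0.55) + 1.036 × √(0.25 + 0.24)]² / 0.10² = 443 per arm.

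443 × 1.5 = 664.5, against the stated 663. 663/0.92 = 720.7, against the stated 720. So the plan's figures reproduce with a normal-theory formula. The 15% loss to follow-up that the section also mentions is not needed to reach 663.

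**2. Type I error of the uncorrected robust Wald z test.** With k = 3 equal centres per arm, the uncorrected robust variance is (k − 1)/k = 2/3 of the unbiased between-centre variance. The difference divided by the square root of the unbiased variance follows approximately t on 6 − 2 = 4 df. Rejecting when |z| > 1.96 is therefore rejecting when |t4| > 1.96 × √(2/3) = 1.600, and P(|t4| > 1.600) = 18.5%.

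Checks, with 240 per centre and event rate 0.5 in both arms:
- Beta-binomial simulation, 200,000 runs per setting: 18.1% to 18.6% for intracluster correlations from 0 to 0.05.
- 4,000 fitted logistic GEEs with exchangeable correlation (intracluster correlation 0.0021): 18.5%.

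The corresponding nominal 95% interval covers about 100 − 18.5 = 81.5%. Its width relative to one using the unbiased variance and the 4-df critical value is 1.600/2.776 = 0.58.

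**3. Other tests that the sentence in the plan would also allow, and their power.** For the difference 0.10, SE = √[(0.25 + 0.24) × 1.5/N]. This gives 0.0333 at N = 663 (noncentrality 3.00) and 0.0320 at N = 720 (noncentrality 3.13). Power is from the noncentral t on 4 df with the critical value shown. The score test was simulated.

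| Variant | Critical value for \|t4\| | Type I error | Power at 663 | Power at 720 |
|---|---|---|---|---|
| Uncorrected robust, z | 1.600 | 18.5% | 90% | 92% |
| Unbiased variance, z | 1.960 | 12.2% | 83% | 86% |
| Uncorrected robust, t on 4 df | 2.776 × √(2/3) = 2.267 | 8.6% | 76% | 79% |
| Mancl-DeRouen, z | 1.960 × √1.5 = 2.400 | 7.4% (7.0% in fitted GEEs) | 72% | 75% |
| Robust score test | – | 5.7% | – | 68% |
| Unbiased variance, t on 4 df (equivalent to a centre-level t-test) | 2.776 | 5.0% | 62% | 65% |
| Mancl-DeRouen, t on 4 df | 2.776 × √1.5 = 3.400 | 2.7% | 46% | 49% |

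The variants that reach 85% power at 720 have a type I error of 12% or more. Those near 5% fall about 17 to 20 points short of 85% at 720. The 720 column counts all 720 as evaluable; after the plan's own 8% attrition the 663 column applies.

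**4. Why two corrections behave differently.** With three equal centres per arm, each centre's leverage is 1/3. Fay-Graubard and Kauermann-Carroll corrections multiply the robust variance by 1/(1 − 1/3) = 1.5, which restores the unbiased value. Mancl-DeRouen multiplies it by 1.5² = 2.25, that is 1.5 times the unbiased value, so adding a 4-df reference over-corrects.

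**5. Permutation.** There are 20 ways to allocate six centres 3 vs 3, so the smallest two-sided p-value is 2/20 = 0.10. Significance at 5% is impossible.

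**6. Unequal recruitment.** If two centres reached only 100 patients instead of 240 (an assumption; the Discussion gives no counts), the uncorrected Wald z test rises to about 20%.

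**The case against.** The strongest reply is that the article does not commit to the uncorrected robust Wald z test. It names GEE and no more, and the variance estimator and degrees of freedom are details that a full protocol or SAP, not shown here, would commonly carry. This stands in part. A reader might infer that the trial's real type I error is 18%; the document does not support that as a fact of the plan. The 18% is conditional on one variant, and others give about 5% to 12%.

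What does not stand is that the matter is therefore only an omitted detail. The article itself fixes the choice of GEE, the six centres, the 5% level and the 85% power. No variant checked delivers that alpha and that power together, so the stated combination is wrong whichever correction an unseen document may name.

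A reader might also infer from the enrolment difficulties that one centre dropped out of the gastroenteritis comparison, leaving 2 vs 3, for which the uncorrected Wald type I error is about 24%. The Discussion reports a lack of such calls at one centre, not an absence of patients, so that figure is not supported.

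The point also does not extend to the mixed-model ANOVA for continuous secondary endpoints. The article states no degrees-of-freedom method for it, and nothing here was calculated for it.

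**Conclusion.** The concern holds in conditional form, and it needs correcting before the analysis. With 3 vs 3 centres, a GEE with uncorrected robust variance and a Wald z test has a type I error of about 18% instead of 5%, and the plan names nothing that would prevent this. A low intracluster correlation is no protection, because the error comes from the number of centres and not from the strength of clustering.

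Independently of which variant is used, the claimed 85% power at 5% alpha is not attainable under the plan's own assumptions. A valid 4-df test has about 62% at 663 and 65% at 720 per arm per indication. These figures assume equal centre sizes, all six centres contributing, 50% vs 40%, and a design effect of 1.5.

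**What to change.** State in the Statistical analyses section that the primary test, and the GEE tests of categorical secondary endpoints, will use a method valid for six clusters. Either of these will do:

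- a t-test on centre-level proportions with df equal to contributing centres minus 2 (4 if all six contribute); covariate adjustment in a first stage is optional and not needed to hold the 5% level;
- GEE with a Fay-Graubard or Kauermann-Carroll type variance correction and a t reference on the same df.

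Report confidence intervals from the same method. Do not pair Mancl-DeRouen with t on 4 df (size about 2.7%, power about 46% at 663), and do not rely on a permutation test (minimum two-sided p = 0.10). If the full protocol or SAP already names a suitable correction, one sentence confirming it settles the test.

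In the Sample size section, restate the power as about 62% at 663 and 65% at 720 per arm per indication.

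The programming cost is small and no data collection changes. The real cost is wider confidence intervals and an openly lower power. Inclusion ended in July 2016 (Trial status), so this can no longer be recovered by adding centres.

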## Discussion

This trial will assess the effectiveness and the cost-effectiveness of a formalised response to calls made for assistance with fever or symptoms of gastroenteritis without seriousness criteria. The inclusion period ended in July 2016. The follow-up is still running and the economic evaluation will start shortly. Two of the centres had several difficulties in enrolling patients. One centre because of a lack of calls made for symptoms of gastroenteritis and the other because of an organisational problem not attributable to the trial. To analyse a potential seasonality effect, the recruitment period stopped at 12 months, as described in the methods section, even if centres had not reach the number of included patients.

### Final report

The final report will adhere to the Consolidated Standards of Reporting Trials (CONSORT) extension for cluster trials.

## Trial status

The inclusion period ended in July 2016.

## Abbreviations

eCRF: Electronic case report form
ED: Emergency Department
fTMA: Formal telephone medical advice
GI: Gastrointestinal
GP: General practitioner
ITT: Intent-to-treat
